## Abstract

**Background:**

Temporomandibular disorder (TMD) is described as a subgroup of orofacial pain with a set of signs and symptoms that involve the temporomandibular joint, masticatory muscles, ears, and neck. TMD can occur unilaterally or bilaterally and approximately 70% of the population is affected with at least one sign. The disorder progresses with orofacial pain, muscle pain involving the masticatory and cervical muscles, joint noises (clicks and pops), joint block, mandibular dysfunction, and headache. The etiology can be abnormal occlusion and/or posture, trauma involving local tissues, repetitive microtrauma, parafunctional habits, and an increase in emotional stress. Studies have demonstrated that phototherapy is an efficient option for the treatment of TMD, leading to improvements in pain and orofacial function.

**Methods:**

The aim of the proposed study is to compare the effects of two sources of photobiomodulation in individuals with TMD. A randomized, controlled, double-blind, clinical trial is proposed, which will involve 80 individuals aged 18–65 years allocated to either a laser group or light-emitting diode (LED) group submitted to 12 sessions of phototherapy. The Research Diagnostic Criteria for TMDs will be used to evaluate all participants. Pain will be measured using the visual analog scale and maximum vertical mandibular movement will be determined with the aid of digital calipers.

**Discussion:**

This study compares the effects of two modalities of laser therapy on the pain and orofacial function of patients with TMD dysfunction. Photobiomodulation and LED therapy are treatment options for reducing the inflammatory process and pain as well as inducing the regeneration of the target tissue.

**Trial registration:**

ClinicalTrials.gov, NCT03257748. Registered on 8 August 2017.

**Electronic supplementary material:**

The online version of this article (doi:10.1186/s13063-018-2444-7) contains supplementary material, which is available to authorized users.

## Background

The temporomandibular joints link the lower jaw (mandible) to the temporal bone of the skull, which is immediately in front of the ear on each side of the head. The flexibility of the joints allows the mandible to move up and down as well as from side to side [1, 2].

Temporomandibular disorder (TMD) is described as a subgroup of orofacial pain with a set of signs and symptoms that involve the temporomandibular joint, masticatory muscles, ears, and neck either unilaterally or bilaterally [2–6]. The signs and symptoms include orofacial pain [2, 8], muscle pain involving the masticatory and cervical muscles, joint noises (clicks and pops), joint block, mandibular dysfunction [8–11], and headache [2, 7, 8]. The etiology can be abnormal occlusion and/or posture, trauma involving local tissues, repetitive microtrauma, parafunctional habits, and an increase in emotional stress [2, 7, 8, 10, 12]. With regard to prevalence, studies report that approximately 70% of the population can have at least one sign of TMD [13–15], but only 10% seek treatment [13, 15]. Pain is the most common symptom and can affect quality of life due to limitations regarding actions such as laughing, eating, speaking, and yawning [3, 10, 14].

Due to the pain and functional limitations inherent to TMD, phototherapy has been investigated and has proven to be an important treatment option for this disorder [1, 4, 5, 7-9, 11, 13, 16, 17]. Photobiomodulation and light-emitting diode (LED) therapy are treatment options for reducing pain and inflammatory processes as well as inducing the regeneration of the target tissue [18–20]. Both types of phototherapy have been suggested for the treatment of inflammatory joint conditions due to the absence of side effects, which are common with the use of non-steroidal anti-inflammatory drugs (NSAIDs) [20]. Studies have reported that lasers and LEDs operating with similar parameters produce equivalent effects [21, 22]. Different theories have been proposed to explain the analgesic action of phototherapy, but no consensus has been reached. Some authors report effects such as biomodulation, the capacity to stimulate cell division, analgesia, modulation of the production of β-endorphins, as well as increases in cortisol and protein synthesis [9, 16–18, 23–27].

Drugs are widely employed for the treatment of pain, but are expensive, which generates high costs in the public health realm, and have limited effectiveness as well as potentially serious side effects, especially when administered for prolonged periods of time. Thus, non-pharmacological, non-invasive resources for pain relief are of the utmost importance and have been widely investigated in the scientific literature.

### Hypothesis

Based on previous studies conducted by different research groups, the proposed study will test the hypothesis that photobiomodulation in the form of low intensity laser compared to LED decreases pain and improves temporomandibular joint function, thereby accelerating the return to activities of daily living.

### Objective

The aim of the proposed study is to analyze the effect of laser therapy and LED therapy on pain and function in patients with TMD and its association with neck pain.

### Expected results

At the end of the study, we expect to find a reduction in pain in the temporomandibular joint and temporal muscle region, and improvement in the function of the temporomandibular joint through photobiomodulation and LED therapy in patients with TMD, with a consequent improvement in their quality of life.

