## Methods / design

### Study design

This protocol is presented in accordance with the 2013 SPIRIT (Standard Protocol Items: Recommendations for Interventional Trials) Statement (see Additional file 1 for the populated SPIRIT Checklist and Fig. 1 for the trial schedule of enrollment, interventions, and assessments in accordance with recommended SPIRIT figure), which was developed to provide guidance in the form of a checklist of recommended items to include in a clinical trial protocol to help improve its content and quality. A randomized, controlled, clinical trial will be conducted at the dentistry and physical therapy clinics of University Nove de Julho (Brazil) involving individuals with TMD distributed between two groups. This protocol study received approval from the Human Research Ethics Committee of University Nove de Julho (São Paulo, Brazil) under process number 1.706.160. All potential participants will receive clarifications regarding the objectives and procedures and those who agree to participate voluntarily will sign a statement of informed consent, as stipulated in Resolution 466/2012 of the Brazilian National Board of Health.

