**Fig. 1 Fig1:**
[figure not shown]
The SPIRIT Statement is important to detail the methodology, ensuring a high quality of clinical trial protocols

The patients will be randomly allocated to either the photobiomodulation or LED group using a set of opaque, sealed, numbered envelopes to ensure concealment. Each envelop will contain a card stipulating to which group the volunteer will be allocated. The participants will then be sent for evaluations (Fig. 2).

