### Interventions

#### Phototherapy

The volunteers will be allocated to two groups:

The sessions will be held in a reserved, noise-free room. The volunteer will be positioned with the Frankfurt plane parallel to the ground. The devices will be covered in disposable plastic wrap to avoid cross-contamination and for hygiene reasons. The operator will wear suitable protective clothing. The skin at the site to be irradiated will have previously been cleaned with 70% alcohol. Both the operator and volunteer will use protective eyewear.

Both groups (laser and LED) will be submitted to eight sessions of phototherapy held twice a week for four weeks, during which only the researcher in charge of programming the phototherapy device will be aware of which treatment is being employed. However, the programmer will not participate in the execution of the treatments, evaluations, or data analysis.

Phototherapy will be applied:Temporomandibular joint region: around the temporomandibular joint;Masseter and temporal muscles: on the masseter and the anterior temporal.

The number of irradiated points will depend on the treatment. Patients in the laser group will have three points irradiated, while those in the LED group will have 36 points irradiated. The parameters that shall be used can be found in Table 2.

**Table 2 Tab2:** Parameters of phototherapy

Parameters	Laser group	LED group
Wavelength (nm)	780	780
Target area (cm^2^)	130	130
Spot area (cm^2^)	43	3.58
Power (mW)	60	5
Irradiation time (s)	600	600
Points irradiated	3	36
Energy per point (J)	36	3
Total energy (J)	108	108
Radiant exposure (J/cm^2^)	0.8	0.8
Irradiance (mW/cm^2^)	1.38	1.38

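### The Expected results credit improvement to both therapies and the Objective names no contrast, but with two active arms only the laser-minus-LED difference is identified

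*Protocol article*

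**What the plan says.** All references are to the protocol article.

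- **Abstract, Methods:** the aim is to "compare the effects of two sources of photobiomodulation in individuals with TMD".
- **Hypothesis:** the study will test whether "photobiomodulation in the form of low intensity laser compared to LED decreases pain and improves temporomandibular joint function". This is also comparative.
- **Objective:** the aim is to "analyze the effect of laser therapy and LED therapy on pain and function in patients with TMD". No contrast between the two is named.
- **Expected results:** the investigators expect to find reduced pain and "improvement in the function of the temporomandibular joint through photobiomodulation and LED therapy in patients with TMD", with better quality of life as a consequence.
- **Study design, allocation:** "The patients will be randomly allocated to either the photobiomodulation or LED group".
- **Interventions, Phototherapy:** "Both groups (laser and LED) will be submitted to eight sessions of phototherapy". No sham, placebo or untreated arm appears anywhere. (The abstract gives 12 sessions. That is a separate inconsistency, and the two places must be reconciled.)
- **Evaluations:** pain on the visual analog scale (VAS) and maximum vertical mandibular movement are measured before and after treatment.
- **Statistical analysis:** ANOVA with the Tukey–Kramer post hoc test for parametric data and Friedman's test otherwise, at the 5% level. No between-group contrast is named.

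**The concern.** The document poses two different questions. One is whether laser and LED differ, which a two-arm randomised trial can answer. The other is whether each therapy reduces pain and improves function, which this trial cannot answer because no patient goes without active light.

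The second question is the one on which the Expected results describe success. Improvement in both arms would meet that expectation whether or not laser differs from LED, so the expected finding says nothing about the stated hypothesis. Patients enter because they have a clinical diagnosis of temporomandibular disorder, and pain is self-rated. Natural course, regression to the mean and placebo response are therefore all plausible sources of improvement.

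Two wrong conclusions are at stake. The first is an efficacy claim for either light source drawn from before–after change. The second is reading a before–after result that is significant in one arm and not in the other as a difference between laser and LED.

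**Working it through.** **Step 1: what the design identifies.** Write the mean change in each arm as

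- laser: L + N
- LED: E + N

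Here L and E are the effects of the light, and N is the non-specific change (natural course, regression to the mean, placebo response). Randomisation makes N the same on average in both arms, provided that blinding keeps the placebo response equal. The difference is (L + N) − (E + N) = L − E, which is identified. Neither L nor E can be separated from N, because no arm receives N alone.

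**Step 2: which question each section asks.**

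| Section | Quantity sought | Identified? |
|---|---|---|
| Abstract aim | L − E | Yes |
| Hypothesis | L − E | Yes |
| Objective | effect of laser and of LED, contrast not named | Only if read as L − E |
| Expected results | improvement through both, so L and E | No |

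**Step 3: which question the analysis answers.** Friedman's test compares related measurements on the same subjects. Each patient belongs to one arm and is measured before and after, so the related measurements are the two time points. On that branch the only named test yields before–after p-values and omits the randomised contrast. The ANOVA branch could carry a between-group term, but none is named.

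**Step 4: the plan's own figure.** The Sample composition section gives a total of 80, SD 9.82 (unit not stated), 5% significance and 80% power, but no target difference. The 80 can therefore be neither reproduced nor refuted. Solved backwards with 40 per arm (ratio assumed) and a two-sided 5% test:

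difference = 9.82 × √(2/40) × (1.960 + 0.842) = 2.196 × 2.802 = 6.15, or 0.63 SD.

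With a one-sided test it is 5.46, or 0.56 SD. The point does not depend on this figure.

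**Step 5: illustration on mouth opening.** Set L = E = 0 and let N = c. The SD is the document's 9.82, taken as the SD at each visit. The change c and the pre–post correlation ρ are assumed. For one arm of 40:

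SD of change = 9.82 × √(2(1 − ρ)); z = c / (SD of change / √40); P(p < 0.05) = Φ(z − 1.96) + Φ(−z − 1.96).

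Example, c = 4 and ρ = 0.5: SD of change 9.82, standard error 1.553, z = 2.576, P = 0.73.

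With independent arms, both are significant with probability P² and exactly one with probability 2P(1 − P).

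| c | ρ | P, one arm | Both arms | Exactly one |
|---|---|---|---|---|
| 2 | 0.3 | 0.19 | 0.04 | 0.31 |
| 2 | 0.7 | 0.38 | 0.15 | 0.47 |
| 4 | 0.3 | 0.59 | 0.34 | 0.49 |
| 4 | 0.7 | 0.91 | 0.84 | 0.16 |
| 6 | 0.3 | 0.90 | 0.82 | 0.17 |
| 6 | 0.7 | 0.999 | 0.998 | 0.002 |

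**Step 6: the same on VAS pain.** All inputs are assumed: 40 per arm, one-sample t-test per arm, identical non-specific improvement in both arms.

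| Improvement (cm) | SD of change (cm) | Both arms | Exactly one |
|---|---|---|---|
| 1.0 | 2.0 | 76% | 23% |
| 1.0 | 2.5 | 48% | 43% |
| 1.0 | 3.0 | 29% | 50% |
| 1.5 | 2.5 | 92% | 8% |

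The between-arm test stays at about 5% in simulation.

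**The case against.** The strongest reply is that the tested question is already comparative. The Hypothesis, the abstract aim and the Discussion all present the study as laser against LED, and the Expected results section is a narrative forecast that sets no endpoint or decision rule. This stands in part. It limits the point to a mismatch of wording and inference. It does not remove it, because the formal Objective still names no contrast and the Friedman branch would not test one.

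A second reply is that the per-arm tests in the illustration are not in the plan. That is correct. The Statistical analysis section plans no one-sample t-tests, and the normal data used in the illustration would go to ANOVA. The tables show only why a before–after p-value cannot be read as efficacy. They do not predict this trial's results.

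A third reply is that reporting detail belongs in an analysis plan that is not shown. That holds for layout and format. It does not hold for the estimand, since no analysis plan can supply an arm that the design lacks.

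Four stronger readings are tempting, and the documents do not support them:

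- **That the word controlled is misused in Study design.** An active comparator is a control, so "A randomized, controlled, clinical trial will be conducted" is accurate.
- **That the Objective itself attributes before–after improvement to each therapy.** It does not. Only the Expected results do. The Objective can be read as loose shorthand for the comparison.
- **That improvement in both arms is close to guaranteed.** Over the assumed ranges, the chance that both arms are significant runs from 0.04 to 0.998.
- **That the trial needs a sham arm.** A head-to-head comparison is legitimate for the stated Hypothesis.

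**Conclusion.** The point holds as a mismatch between the stated claims and the design. With two active arms, only the laser-minus-LED difference is identified. The Expected results attribute improvement to both therapies, the Objective leaves the contrast unnamed, and the non-parametric analysis would not test it. If the text were followed as written, an unsupported efficacy conclusion for each arm could result.

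The conclusion rests on the absence of a sham or untreated arm, which the document fixes, and on no numerical assumption. The illustrative probabilities rest on assumed changes, correlations and VAS SDs, on 40 per arm, and on separate within-arm tests that the plan does not specify. The randomised comparison is sound as a design, and arms and sample size need no change on this account.

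**What to change.** 1. **Objective:** restate it as estimating the difference between laser and LED (laser minus LED) in pain and in mandibular opening.
2. **Expected results:** express the expectation as that same between-arm difference, in line with the Hypothesis, and remove the attribution of improvement to each therapy.
3. **Statistical analysis:** state that conclusions rest on the between-arm contrast, on the parametric and the non-parametric branch alike. State also that within-arm change is descriptive and that no efficacy claim for either therapy will be drawn from it. Friedman's test cannot carry that contrast, so the non-parametric branch needs a method that compares the two independent groups.

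The cost is rewording in three sections and the loss of an efficacy claim that the design cannot support. Arms, randomisation, sample size and assessments are unchanged.

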## Methods / design

### Study design

This protocol is presented in accordance with the 2013 SPIRIT (Standard Protocol Items: Recommendations for Interventional Trials) Statement (see Additional file 1 for the populated SPIRIT Checklist and Fig. 1 for the trial schedule of enrollment, interventions, and assessments in accordance with recommended SPIRIT figure), which was developed to provide guidance in the form of a checklist of recommended items to include in a clinical trial protocol to help improve its content and quality. A randomized, controlled, clinical trial will be conducted at the dentistry and physical therapy clinics of University Nove de Julho (Brazil) involving individuals with TMD distributed between two groups. This protocol study received approval from the Human Research Ethics Committee of University Nove de Julho (São Paulo, Brazil) under process number 1.706.160. All potential participants will receive clarifications regarding the objectives and procedures and those who agree to participate voluntarily will sign a statement of informed consent, as stipulated in Resolution 466/2012 of the Brazilian National Board of Health.

**Fig. 1 Fig1:**
[figure not shown]
The SPIRIT Statement is important to detail the methodology, ensuring a high quality of clinical trial protocols

The patients will be randomly allocated to either the photobiomodulation or LED group using a set of opaque, sealed, numbered envelopes to ensure concealment. Each envelop will contain a card stipulating to which group the volunteer will be allocated. The participants will then be sent for evaluations (Fig. 2).

**Fig. 2 Fig2:**
[figure not shown]
*Flow chart* illustrating phases of study (CONSORT, 2010)

### Participants

Male and female individuals aged 18–65 years with a clinical diagnosis of TMD based on the Research Diagnostic Criteria for Temporomandibular Disorders (RDC/TMD) will be selected to participate in the study. No restrictions will be imposed with regard to race.

The volunteers will be informed of all procedures and sign a statement of informed consent before the onset of the study.

### Inclusion criteria

Clinical diagnosis of TMD, separated by the degrees of this function based on the Research Diagnosis Criteria for Temporomandibular Disorders, as shown in Table 1;

**Table 1 Tab1:** Diagnostic subgroups according to RDC/TMD

Group I Muscle diagnoses	
Ia – myofascial pain	
Ib – myofascial pain with limited opening	
Group II Disk displacement	
IIa – disk displacement with reduction	
IIb – disk displacement without reduction with limited opening	
IIc – disk displacement without reduction without limited opening	
Group III Arthralgia, osteoarthritis, and osteoarthrosis	
IIIa – arthralgia	
IIIb – osteoarthritis of temporomandibular joint	
IIIc – osteoarthrosis of temporomandibular joint	Age 18–65 years;Presence of at least 20 functional teeth, at least three being molars.

### Exclusion criteria

Dentofacial anomalies;Currently in orthodontic or orthopedic treatment for the jaw;Currently undergoing psychological treatment;Use of muscle relaxant or anti-inflammatory agent.

### Sample composition

The sample size was calculated based on studies found in the literature using maximum vertical mandibular movement as the basis, with a standard deviation of 9.82, a 5% significance level (*p* < 0.05), and 80% test power. The sample was determined to be 80 individuals, who will be allocated to two groups.Step 1 – Recruitment for the selection of patients who will participate in the study. The patients will receive clarifications regarding the objectives and procedures and those who agree to participate voluntarily will sign a statement of informed consent.Step 2 – The selected patients will receive an envelope containing a card stipulating to which group they will be allocated. The patients will not be aware of the content of the envelope.

### Interventions

#### Phototherapy

The volunteers will be allocated to two groups:

The sessions will be held in a reserved, noise-free room. The volunteer will be positioned with the Frankfurt plane parallel to the ground. The devices will be covered in disposable plastic wrap to avoid cross-contamination and for hygiene reasons. The operator will wear suitable protective clothing. The skin at the site to be irradiated will have previously been cleaned with 70% alcohol. Both the operator and volunteer will use protective eyewear.

Both groups (laser and LED) will be submitted to eight sessions of phototherapy held twice a week for four weeks, during which only the researcher in charge of programming the phototherapy device will be aware of which treatment is being employed. However, the programmer will not participate in the execution of the treatments, evaluations, or data analysis.

Phototherapy will be applied:Temporomandibular joint region: around the temporomandibular joint;Masseter and temporal muscles: on the masseter and the anterior temporal.

The number of irradiated points will depend on the treatment. Patients in the laser group will have three points irradiated, while those in the LED group will have 36 points irradiated. The parameters that shall be used can be found in Table 2.

**Table 2 Tab2:** Parameters of phototherapy

Parameters	Laser group	LED group
Wavelength (nm)	780	780
Target area (cm^2^)	130	130
Spot area (cm^2^)	43	3.58
Power (mW)	60	5
Irradiation time (s)	600	600
Points irradiated	3	36
Energy per point (J)	36	3
Total energy (J)	108	108
Radiant exposure (J/cm^2^)	0.8	0.8
Irradiance (mW/cm^2^)	1.38	1.38

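### The operator is said not to know the arm, but the procedure described differs by arm (3 points or 36) and no masking at delivery is described

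*Protocol article*

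**What the plan says.** The abstract of the Protocol article states: "A randomized, controlled, double-blind, clinical trial is proposed". The Study design section describes the trial as randomized and controlled and does not use the blinding label.

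The Phototherapy section says who knows the allocation: "only the researcher in charge of programming the phototherapy device will be aware of which treatment is being employed". It adds that "the programmer will not participate in the execution of the treatments, evaluations, or data analysis". Someone else therefore delivers the treatment, and that person is stated to be unaware of the arm.

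The same section then says: "The number of irradiated points will depend on the treatment". It continues: "Patients in the laser group will have three points irradiated, while those in the LED group will have 36 points irradiated". Table 2 gives spot areas of 43 cm² (laser) and 3.58 cm² (LED) and powers of 60 mW and 5 mW. Other rows are equal in the two arms: "Wavelength (nm) 780 780", "Irradiation time (s) 600 600" and "Total energy (J) 108 108". The one covering mentioned for the devices is plastic wrap, and its stated purpose is hygiene.

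Blinding of other roles is stated separately. Under Sample composition, patients do not know what their envelope contains. Under Reliability of examiner, both the initial examiner and the one who re-evaluates after treatment are blinded.

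**The concern.** Two statements in one section do not fit together. The operator is said not to know the arm, yet the number and size of the irradiated points are set by the arm. Unless something hides this difference, giving the treatment reveals it.

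Both arms are active and the hypothesis is directional, with laser expected to do better than LED. An operator who knows the arm can pass on expectation over repeated sessions. Pain is marked by the participant on a visual analogue scale, so a blinded examiner does not shield it. Maximum opening is measured by a blinded examiner, but the participant is asked to open as wide as possible. It depends on effort and is only partly shielded. If session length also differed between arms, contact time and attention would be mixed with the light source. An unqualified double-blind label would then claim more protection from bias than the described design gives.

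**Working it through.** **Inputs** (Table 2, laser / LED): power 60 / 5 mW; time 600 / 600 s; points 3 / 36; spot area 43 / 3.58 cm²; target area 130 / 130 cm²; energy per point 36 / 3 J; total energy 108 / 108 J; radiant exposure 0.8 J/cm²; irradiance 1.38 mW/cm².

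**Step 1: reproduce the table.**
- Energy per point = power × time. Laser: 0.060 W × 600 s = 36 J. LED: 0.005 W × 600 s = 3 J. Both match.
- Total energy = energy per point × points. Laser: 36 × 3 = 108 J. LED: 3 × 36 = 108 J. Both match.
- Area covered = spot × points. Laser: 43 × 3 = 129 cm². LED: 3.58 × 36 = 128.9 cm². Either set of points fills the 130 cm² target almost completely.
- Radiant exposure = 108 / 130 = 0.83 J/cm², printed as 0.8.

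The energy rows hold only if every point receives 600 s.

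**Step 2: does the table say whether points are treated in turn or together?** Irradiance is the only row that might.
- All points emitting at once over the whole target: (3 × 60) / 130 = 180 / 130 = 1.385 for laser; (36 × 5) / 130 = 1.385 for LED.
- One point over an equal share of the target: 60 / (130/3) = 60 / 43.33 = 1.385; 5 / (130/36) = 5 / 3.61 = 1.385.
- One point over the printed spot area: 60 / 43 = 1.395; 5 / 3.58 = 1.397.

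The printed 1.38 fits the first two. When points tile the target, per-point and whole-target irradiance are algebraically the same. The gap to the third is about 0.01, which is of the size produced by rounding 43.33 to 43 (and 43 / 12 = 3.58). The row cannot settle the order of delivery.

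**Step 3: consequences under each reading.**

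| Delivery | Laser session | LED session | Who could tell the arms apart |
|---|---|---|---|
| Points in turn | 3 × 600 = 1,800 s = 30 min | 36 × 600 = 21,600 s = 6 h | Operator and participant |
| Points together | 600 s = 10 min | 600 s = 10 min | Operator, unless the layout is masked; the participant not necessarily |

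**Step 4: set the statements side by side.** The operator's stated ignorance of the arm is compatible with 36/3 = 12 times as many points in one arm only if the operator sees and does the same thing in both. That would need, for example, one preset and masked applicator. The article describes no such arrangement, and it speaks of the device in the singular when programming is discussed but in the plural when covering is discussed.

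**The case against.** The strongest reply is that loss of operator blinding is inferred. The article nowhere says that the operator places 3 or 36 spots by hand. A programmed source with preset emission, serving both arms, would fit the sentence about the programmer and the equal time, target area and total energy. A journal article is also condensed, and applicator housing may be described in the full protocol. This stands to the extent that one cannot say the operator must be unblinded. It does not remove the problem: the issue is not a missing detail but two printed statements that conflict unless an undescribed arrangement is supplied.

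A second reply is that the double-blind label can rest on participants and examiners, whose blinding is stated elsewhere. This also stands for the label, provided delivery is simultaneous. It does not rescue the sentence that confines knowledge of the arm to the programmer.

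A reader might infer more: that blinding has failed in every session, that LED sessions last six hours, or that the trial should be called assessor-blind. The documents support none of these. The six-hour figure holds only if points are treated in turn, which is not stated. No figure for the share of sessions unblinded can be derived. Dropping participant blinding from the label would remove something that the point count alone does not disprove.

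**Conclusion.** The concern holds in this form: as described, operator blinding is not feasible, because the procedure is arm-dependent (3 points of 43 cm² or 36 points of 3.58 cm²) and no masking at delivery is given. Participant blinding is in doubt only if points are treated in turn, when sessions would last 30 minutes against 6 hours. If points are treated together, both sessions last 10 minutes and the clear risk is confined to the operator. Blinding of the two examiners is not contradicted.

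This assumes that the powers in Table 2 are per point, which the energy rows confirm, and that no common masked applicator exists beyond what is written. The size of any resulting bias in pain or opening cannot be calculated from the document.

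**What to change.** Reconcile the statements in the Phototherapy section and Table 2 by saying whether the points are irradiated simultaneously or in sequence. Then take one of two routes.

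1. If one masked applicator with the same visible procedure serves both arms, describe it. The sentence on who knows the treatment can then stay.
2. If not, replace that sentence and the unqualified double-blind label with a list of roles: both examiners blinded, participants blinded if delivery is simultaneous, operator not blinded. Interpret both participant-marked pain and effort-dependent maximum opening with that limitation.

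Making the calliper measure the main result would not solve the problem, since effort can be influenced too. Placing both applicators on every participant is of unproven feasibility, because each arm's points already fill the target area.

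Either route costs only wording. The downside of the second is a less favourable description of the blinding.
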